### Interventions

#### Explanation for the choice of comparators {6b}

This study aims to test the effectiveness of the Healthy Mind intervention, which is provided in addition to the existing annual chronic care consultation. Therefore, usual care is the most appropriate comparator and acts as the control group.

#### Intervention description {11a}

##### Method used for intervention development

The intervention was developed using the UK Medical Research Council framework for developing complex interventions [20]. The intervention development process consisted of two phases: the initial development phase and the feasibility testing phase. Three approaches for intervention development were applied: the evidence-and-theory-based approach, the target population-centred approach, and the implementation approach [21]. During the initial phase, intervention development was informed by literature reviews, insights from a small-scale study testing PST in the general practice setting, and by attending to the existing frames in general practice [22]. In the feasibility testing phase, perspectives from healthcare providers and patients further informed the intervention development [16]. Our programme theory was refined throughout the development phase, and the intervention was adjusted accordingly.

##### Problem-solving therapy (PST)

PST is a well-established psychological treatment aiming at improving the patient’s problem-solving and coping skills [23, 24]. The assumption is that a person’s problem-solving and coping skills influence whether negative life events result in psychological symptoms, such and depression and anxiety [23, 25]. The core element of PST is training of problem-solving and coping skills by following five sequential steps: (1) listing problems and choosing one to address, (2) defining the problem in question, (3) generating solutions, (4) analysing pros and cons for each solution and choosing one, and (5) planning and undertaking the implementation of the solution. The PST provider facilitates and guides the process, while the patient takes an active role in deciding which topics to address, generating solutions, and planning and undertaking the implementation of the chosen solution. This behavioural activation is considered the pivotal component of the treatment. Patients learn to cope with their problems in a rational and systematic manner, gaining empowerment through experiential learning, realising their ability to manage encountered challenges [26].

##### The healthy mind intervention

All patients with T2D and/or CHD attending annual chronic care consultations in general practice are screened for poor mental well-being using the WHO-5 Well-Being Index (WHO-5) [19], described in detail in “Plans for assessment and collection of outcomes {18a}” section and in Table 1. In the intervention protocol, patients with a WHO-5 score < 50 points are offered PST provided by either the trained GP or practice staff. A booklet guiding patients through the five sequential steps of PST, facilitated by the healthcare professional, is provided. The booklet is designed by the research team based on the insights from the feasibility study [16]. Patients are offered up to seven 30-min PST sessions. In the control protocol, patients receive the usual care.

**Table 1 Tab1:** Participant timeline

Time point	Baseline	During or immediately after the intervention	6 months	12 months
**Enrolment**				
**Eligibility screening**	X			
**Informed consent**	X			
**WHO-5 screen**^a^	X			
**Intervention**				
**Problem-solving therapy (1–7 sessions)**		X		
**Assessments**				
Primary outcome				
**PHQ-9**	X		X	X
Secondary outcomes				
**WHO-5**	X		X	X
**GAD-7**	X		X	X
**PAID-5**^b^	X		X	X
**HbA1c**^b^	X			X
**Total cholesterol**	X			X
**LDL**	X			X
Process outcomes				
Implementation				
**Fidelity**		X		
**Dose**		X		
**Reach**		X		
Mechanisms of impact				
**Mediators**		X		
**Unintended consequences**		X		

^a^Only patients with WHO-5 point score < 50 proceed in the study

^b^Only patients with T2D

##### PST training course

Before transitioning to the intervention protocol, healthcare professionals attend a 2-day PST course. The course is designed on the basis of knowledge from a previous small-scale study and further refined by insights from our feasibility study [16, 22]. Healthcare professionals are encouraged to prepare for the course by watching a 30-min video that demonstrates how PST can be delivered.

The training course comprises both a theoretical component and a component focusing on implementation. Two psychologists with expertise in PST facilitate the theoretical component, which includes lectures on PST in combination with hands-on exercises, including role play, to familiarise participants with PST and ensure that they develop sufficient skills to deliver the intervention after the course. Two members of the research team facilitate the implementation component where participants will formulate specific implementation strategies tailored to their particular general practices to ensure that the intervention is properly integrated into each participating general practice.

#### Criteria for discontinuing or modifying allocated interventions {11b}

Patients may discontinue participation at any time. The exclusion criteria ensure that patients with severe psychopathology (psychosis, suicidal mental state, or dementia) are not invited to participate in the study. If a patient develops severe psychopathological symptoms during the study, the intervention is terminated immediately, and relevant standard treatment is initiated. If a patient withdraws from the study, data collected until the withdrawal will be part of the study.

#### Strategies to improve adherence to interventions {11c}

During the PST course, healthcare providers are trained to deliver the intervention with high fidelity. The booklet used during PST sessions is designed to support adherence to the methodology of PST and facilitate patient involvement.

#### Relevant concomitant care permitted or prohibited during the trial {11d}

All usual care is allowed in both the control and the intervention group, including medical treatment of mental illness and referral to mental health specialists, e.g., a psychologist or psychiatrist.

#### Provisions for post-trial care {30}

Patients retain their usual continuous free and equal access to general practice prior to, during, and after the intervention.

### Outcomes {12}

A programme theory was created to identify anticipated mental, somatic, and process outcomes of the Healthy Mind intervention.

#### Primary outcome

The primary outcome is the mean change in depressive symptoms measured with the nine-item Patient Health Questionnaire (PHQ-9) from baseline to 6 and 12 months [27]. The PHQ-9 questionnaire is validated and frequently used in similar studies, facilitating comparison with previous studies. The PHQ-9 score was chosen as the primary outcome to maintain independence from the WHO-5 score, the measure used at patient inclusion. This decision was made to ensure the internal validity of the study.

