#### Sample size {14}

The sample size was calculated according to the following assumptions: We expect 20% of patients with T2D and/or CHD who attend annual chronic care consultations to decline participation or be excluded from the study. We expect 15% of participating patients to report reduced mental well-being (WHO-5 score < 50 points), and 20% of patients participating in the study are expected to be lost to follow-up after 12 months. The intraclass correlation coefficient (ICC) is conservatively estimated at 0.05, reflecting a realistic expectation that a mental outcome is likely to show a larger dependence on the individual general practice than somatic outcomes, where an ICC of 0.01 is often applied. To achieve a significance level of 5% and a power of 90%, the study is required to include a total of 188 patients.

In Denmark, the size of a general practice depends on its number of practice capacities. Each general practice capacity accommodates approximately 1600 patients, with an average of 2.5 practice capacities per practice. Based on these assumptions, we need to include at least 35 practice capacities (corresponding to 14 average-size general practices) to be able to include 188 patients over a 1-year study period.

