### Data collection and management

#### Plans for assessment and collection of outcomes {18a}

Information about patients is entered into the Healthy Mind website database by healthcare professionals upon enrolment. For patients with a WHO-5 score > 50 points, sex, age, and diagnosis (T2D and/or CHD) are registered. For patients with a WHO-5 score < 50 points, additional registration of social security number, name, contact information, and WHO-5 score is made.

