##### Mental health outcomes

Upon enrolment, an automatically generated link to a questionnaire is sent out to participating patients with a WHO-5 score < 50 points. The questionnaire assesses the primary and secondary mental health outcomes as described above. This link is sent via email/SMS at baseline, as well as after 6 and 12 months. Reminders are sent to non-responders by email/SMS after 1 and 2 weeks, followed by a reminder telephone call after 3 weeks. Patients who are unable to access the electronic questionnaire are provided with an identical paper version at baseline and receive follow-up paper questionnaires by mail after 6 and 12 months. The questionnaires are forwarded to the research team and entered manually into the Healthy Mind database by a data manager independent of the research team. Non-responders to mailed questionnaires receive a reminder telephone call after 3 weeks. The Healthy Mind database mandates that all questionnaire items must be completed before submission, and duplicate registrations cannot be entered, ensuring comprehensive and accurate registrations. More detail on questionnaire properties is provided in Table 2.

**Table 2 Tab2:** Overview of mental health outcomes in questionnaires at baseline and after 6 and 12 months

Questionnaire	Number of items	Range	Cut-off values	Measure
**PHQ-9**^a^	9	0–27	0–5: no depression 5–10: mild depression 10–15: moderate depression 15–20: moderately severe depression > 20: severe depression	Depressive symptoms
**GAD-7**^a^	7	0–21	0–4: minimal anxiety 5–9: mild anxiety 10–14: moderate anxiety > 15: severe anxiety	Anxiety symptoms
**PAID-5**^b^	5	0–20	> 7: elevated diabetes distress	Diabetes distress
**WHO-5**^c^	5	0–100	< 50: impaired mental well-being	Mental well-being

^a^4-point Likert scale (0 = not at all; 3 = nearly all of the time)

^b^5-point Likert scale (0 = not a problem; 4 = serious problem)

^c^6-point Likert scale from (0 = none of the time; 5 = all of the time)

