## Statistical methods

### Statistical methods for primary and secondary outcomes {20a}

#### Primary outcome

The comparative analysis will estimate the mean change in PHQ-9 score from baseline to follow-up at 6 and 12 months. A linear mixed model will be used, adjusting for patients’ age, gender, and socioeconomic status. The cluster effect by general practice and the correlation between repeated measurements on the same patient over time will be taken into account in the multilevel analysis [34].

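### The primary PHQ-9 analysis is worded as change from a post-enrolment baseline form without baseline adjustment; a joint baseline-adjusted model would keep every patient with any PHQ-9 and be more precise

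*Protocol article*

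**What the plan says.** Outcomes {12} defines the primary outcome as "mean change in depressive symptoms measured with the nine-item Patient Health Questionnaire (PHQ-9) from baseline to 6 and 12 months". Statistical methods {20a} repeats this as the quantity to be estimated: "The comparative analysis will estimate the mean change in PHQ-9 score from baseline to follow-up at 6 and 12 months". The model is a linear mixed model with age, gender and socioeconomic status as covariates. It allows for clustering by practice and for correlation between a patient's repeated measurements. No baseline score is among the covariates, and the article does not say whether the baseline PHQ-9 is one of the repeated outcomes or is subtracted beforehand.

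Eligibility {10} rests on a WHO-5 score below 50 and not on a PHQ-9 value. The PHQ-9 follows later: "Upon enrolment, an automatically generated link to a questionnaire is sent out to participating patients with a WHO-5 score < 50 points". Non-return is foreseen: "Reminders are sent to non-responders by email/SMS after 1 and 2 weeks, followed by a reminder telephone call after 3 weeks". There is also a paper route: "Patients who are unable to access the electronic questionnaire are provided with an identical paper version at baseline". The screening WHO-5, by contrast, is entered by the practice for every patient below 50: "additional registration of social security number, name, contact information, and WHO-5 score is made".

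The only loss named in Sample size {14} is at the end of follow-up: "20% of patients participating in the study are expected to be lost to follow-up after 12 months". Section {20c} adds multiple imputation as a sensitivity analysis to the intention-to-treat analysis.

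**The concern.** Two things are at stake.

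- **Who is analysed.** An individual change score needs both values. A patient who never returns the first form but answers at 6 or 12 months has usable follow-up data and no change score. If the model is fitted to change scores, the analysis called intention-to-treat silently omits that patient, and the sample size makes no mention of such a loss.
- **How well the data are used.** Even with complete baselines, subtracting the baseline value is not the most efficient use of it. Adjusting for it is more precise whenever the correlation between baseline and follow-up is below 1 and the variances are similar. The stated covariate list leaves that gain unused.

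**Working it through.** **Inputs.** From Sample size {14}: 188 patients, 20% lost at 12 months, ICC 0.05, 14 practices, 5% significance (taken as two-sided, since sidedness is not stated) and 90% power. Assumed, because the article gives no figure: baseline non-return m of 5–20%, independent of later loss, and a correlation ρ of 0.5–0.65 between baseline and follow-up PHQ-9.

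**1. The plan's own figure.** The 188 cannot be reproduced, because no PHQ-9 difference or standard deviation is given. I therefore take 188 as the number enrolled and let 188 × 0.8 = 150.4 patients at 12 months have exactly 90% power.

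**2. Loss if only observed change scores are analysed.** The number analysed is n = 150.4 × (1 − m).

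- Ignoring clustering, power is Φ(3.2416 × √(1 − m) − 1.960), where 3.2416 = 1.960 + 1.2816.
- With clustering, the effective number is n / [1 + (n/14 − 1) × 0.05], and √(1 − m) is replaced by the root of its ratio to 101.1, the effective number at m = 0. This is a parallel-group design effect, used as an approximation to the stepped-wedge design.

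| m | n at 12 months | SE factor 1/√(1 − m) | Power, no clustering | Effective n | Power, clustered |
|---|---|---|---|---|---|
| 0 | 150.4 | 1.000 | 90.0% | 101.1 | 90.0% |
| 5% | 142.9 | 1.026 | 88.5% | 97.8 | 89.0% |
| 10% | 135.4 | 1.054 | 86.8% | 94.4 | 87.9% |
| 15% | 127.8 | 1.085 | 84.8% | 90.9 | 86.7% |
| 20% | 120.3 | 1.118 | 82.6% | 87.2 | 85.3% |

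**3. Does a repeated-outcome model keep these patients?** This was simulated with 60 runs, 188 patients, 14 practices, 15% of baselines and 20% of each follow-up missing at random, and individual allocation rather than the stepped-wedge schedule. About 27 patients per run had follow-up but no baseline.

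- With baseline as a repeated outcome, 187 patients contributed and the mean standard error of the 12-month effect was 0.69.
- Restricted to patients with a baseline, 160 contributed and it was 0.74.
- Both estimates were close to the true −2.0 (−1.98 and −1.99), as expected when values are missing at random.

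**4. Change score against baseline-adjusted joint model.** This is at patient level, one follow-up, equal variances, clustering ignored and a common baseline mean. In the same units the variances are:

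- change score: 2(1 − ρ)/(1 − m)
- joint model: 1/[(1 − m)/(1 − ρ²) + m]

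| ρ | m | Change score | Joint model | SE reduction 1 − √ratio |
|---|---|---|---|---|
| 0.50 | 0 | 1.000 | 0.750 | 13.4% |
| 0.65 | 0 | 0.700 | 0.578 | 9.2% |
| 0.50 | 5% | 1.053 | 0.759 | 15.1% |
| 0.50 | 20% | 1.250 | 0.789 | 20.5% |
| 0.65 | 5% | 0.737 | 0.590 | 10.5% |
| 0.65 | 20% | 0.875 | 0.631 | 15.1% |

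With m = 0 the ratio is (1 + ρ)/2, which is below 1 for every ρ below 1. In that case a repeated-outcome model with a separate baseline mean per condition gives the same contrast as the change score, so the 9–13% gain applies under either reading of {20a}. With 5–20% of baselines missing, the gain over change scores is about 10–20%. A slightly different approximation gives about 9–19%, a difference that is immaterial beside the assumptions.

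**The case against.** The strongest reply is that {20a} already plans a mixed model with correlated repeated measurements. Mean change can be a contrast estimated by that model, so no individual change score is needed and no patient is lost. How baseline enters the model is ordinary analysis-plan content, and that plan is not shown. This stands. A reader might infer that patients without a baseline form cannot be scored or are excluded, but nothing in the article says so; their follow-up PHQ-9 can be scored, and the planned imputation could cover a missing baseline.

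Baseline non-return is also worked against by two reminders, a telephone call and a paper form, and patients who never answer the first form may largely be those already counted in the 20%. That stands too, so the power figures are illustrations.

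A reader might also infer bias, because intervention patients have more visits at which a form could be prompted. The article describes no such prompting and gives no return rates by condition, so any size put on the bias would be invented.

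Nor is leaving the screening WHO-5 out of the primary model an error. Its range is cut off by the entry criterion, it cannot replace a PHQ-9 baseline, and the separation is deliberate: "The PHQ-9 score was chosen as the primary outcome to maintain independence from the WHO-5 score, the measure used at patient inclusion".

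Finally, a common baseline mean is not guaranteed here, because unblinded staff recruit patients after their practice has been allocated. That is a fair limit on the remedy and calls for a sensitivity analysis. It does not rescue the unadjusted change.

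**Conclusion.** The point holds as an inexpensive improvement. It is not an error that invalidates the plan.

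The endpoint and the estimated quantity are worded as change from a baseline requested only after enrolment, with no baseline adjustment. One admissible reading loses enrolled patients from the primary analysis. At an assumed 5–20% non-return independent of later loss, power falls to about 89–85% with clustering, or 88–83% without it. The other reading loses nobody.

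Both readings forgo the gain from baseline adjustment. Against change scores, the joint model lowers the standard error by about 9–13% with complete baselines and about 10–20% with 5–20% missing. These figures rest on assumed correlations of 0.5–0.65, equal variances, no clustering and equal baseline means. The non-return rate is unknown, so the precision gain is the firmer part of the case.

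**What to change.** - In {20a}, state that PHQ-9 at baseline, 6 and 12 months are analysed jointly as outcomes in the linear mixed model, with one baseline mean shared by both conditions. The baseline-adjusted differences between conditions at 6 and 12 months are the effects.
- State that every enrolled patient with any PHQ-9 value is included.
- Because recruitment follows allocation and staff are unblinded, report baseline PHQ-9 and baseline-form return by condition. Give the same model without the common-mean constraint as a sensitivity analysis.
- Use the same approach for GAD-7, PAID-5 and WHO-5. Table 1 lists a WHO-5 screen and a WHO-5 assessment separately at baseline. Name the questionnaire score as the WHO-5 baseline, since the screening score was selected to lie below 50 and is prone to regression to the mean.
- The screening WHO-5 may be added to the imputation model as an auxiliary variable; this is optional.

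The cost is analysis wording only. All the data are already planned for collection, and patients and practices have nothing extra to do.

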**Methods:**

A stepped-wedge cluster-randomised controlled trial with 1-year follow-up will be conducted in Danish general practice. At the annual chronic care consultation, patients with type 2 diabetes and/or chronic ischaemic heart disease will be screened for poor mental well-being. Patients in the control group will be offered usual care while patients in the intervention group will be offered treatment with PST provided by general practitioners (GPs) or general practice staff, such as nurses, who will undergo a 2-day PST course before transitioning from the control to the intervention group. The primary outcome is change in depressive symptoms after 6 and 12 months. Secondary outcomes include change in mental well-being, anxiety, and diabetes distress (patients with type 2 diabetes) after 6 and 12 months as well as change in total cholesterol levels, low-density lipoprotein (LDL) levels, and blood glucose levels (patients with diabetes) after 12 months. Process outcomes include measures of implementation and mechanisms of impact. We aim to include a total of 188 patients, corresponding to approximately 14 average-sized general practices.

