### Interim analyses {21b}

PST is a well-established treatment, which is considered safe and not expected to result in potentially serious adverse outcomes. Thus, no interim analyses are planned.

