#### Dissemination plans {31a}

A minimum of three published articles in international peer-reviewed journals reporting on mental health outcomes after 6 months, mental and somatic outcomes after 12 months, and a process evaluation are expected. Reportings from the study will be based on the CONSORT statement extension on stepped cluster-randomised trials [35]. The study will be presented at multiple national and international conferences. Study results will be communicated to healthcare providers through professional magazines and to the public through social media and patient organisations.

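### The primary outcome has two time points, 6 and 12 months, and no rule for combining them, so the stated 5% significance level is not guaranteed

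*Protocol article*

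**What the plan says.** Three places in the protocol article define the primary outcome, and all three carry both time points.

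- Abstract, Methods: "The primary outcome is change in depressive symptoms after 6 and 12 months".
- Outcomes {12}, Primary outcome: the mean change in depressive symptoms "measured with the nine-item Patient Health Questionnaire (PHQ-9) from baseline to 6 and 12 months".
- Statistical methods {20a}, Primary outcome: "The comparative analysis will estimate the mean change in PHQ-9 score from baseline to follow-up at 6 and 12 months". The model is a linear mixed model, and "The cluster effect by general practice and the correlation between repeated measurements on the same patient over time will be taken into account".

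Sample size {14} gives one error level and one power: "To achieve a significance level of 5% and a power of 90%, the study is required to include a total of 188 patients". It does not say which time point these refer to. Its only attrition figure is that "20% of patients participating in the study are expected to be lost to follow-up after 12 months".

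Dissemination plans {31a} expects at least three articles, "reporting on mental health outcomes after 6 months, mental and somatic outcomes after 12 months", plus a process evaluation. The primary outcome is thus to be reported in two papers.

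**The concern.** A single 5% level describes one primary comparison, but the outcome definition supplies two and does not rank or combine them. Each of the two planned articles could present its own PHQ-9 result as the trial's primary finding at 5%.

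Two things are at stake. First, the article does not exclude counting success at either time point, and under that reading the chance of a false-positive primary claim exceeds 5%. Second, if PHQ-9 differs between groups at 6 months but not at 12, or the reverse, nothing says whether the trial is positive. The trial is unblinded and its primary outcome is patient-reported, so a rule chosen after the 6-month results are known would carry little weight.

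**Working it through.** **Inputs from the article.** Two primary time points (Outcomes {12}); significance level 5%, power 90%, 188 patients, ICC 0.05, 20% loss at 12 months, 14 practices (Sample size {14}).

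**Assumptions.** The 5% is two-sided (sidedness is not stated). The correlation ρ between the 6- and 12-month test statistics is not given, so a range is shown.

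**Step 1: the plan's own figure.** The 188 cannot be reproduced, because no PHQ-9 difference or standard deviation is stated. Only the implied standardised difference can be solved for, using a simple two-group approximation:

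d = (1.960 + 1.282) × √(4 × DE / n), with DE = 1 + (m − 1) × 0.05

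- With 20% loss and 14 clusters: n = 188 × 0.8 = 150.4, m = 150.4/14 = 10.74, DE = 1.487, d ≈ 0.64.
- Counting each practice's control and intervention periods as separate clusters (28): m = 5.37, DE = 1.219, d ≈ 0.58.
- With no loss and no clustering: d = 3.242 × √(4/188) ≈ 0.47.

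None of this shows which time point the 188 was meant for.

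**Step 2: false-positive chance if either time point suffices.**

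Error = 1 − P(|Z₁| < 1.96 and |Z₂| < 1.96), with Z₁ and Z₂ bivariate normal with correlation ρ. For ρ = 0 this is 1 − 0.95² = 9.75%.

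| ρ (assumed) | Chance of at least one false positive |
|---|---|
| 0 | 9.75% |
| 0.5 | 9.07% |
| 0.6 | 8.75% |
| 0.7 | 8.35% |
| 0.8 | 7.81% |
| 0.9 | 7.04% |

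The Bonferroni upper bound is 10%. The value falls to 5% only as ρ reaches 1.

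**Step 3: what each possible rule would do.**

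- *One time point primary, the other tested only if the first is significant:* error stays at 5% for any ρ, and 188 is unchanged.
- *Both required:* error is at most 5%. If power is 90% at each time point, power for both is about 83% (ρ = 0.5) to 87% (ρ = 0.9).
- *2.5% at each:* error is at most 5%. Power per time point falls to Φ(1.960 + 1.282 − 2.241) = Φ(1.00) ≈ 84%. Restoring 90% multiplies the sample by (2.241 + 1.282)² / (1.960 + 1.282)² ≈ 1.181, and 188 × 1.181 ≈ 222.1, so 223 patients.

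The rules differ in both error and power, so the choice is not a formality.

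**The case against.** The strongest reply is that the article speaks of estimating, not of two separate tests. One longitudinal mixed model could yield a joint test, an averaged effect or two contrasts, and nothing says that either result alone is enough. That stands. A reader might infer that the 5% level is in fact broken, but the text does not support this: under a joint test or a both-required rule, error is at most 5%. The mixed model does not settle the matter, however. Allowing for within-patient correlation gives valid standard errors for each contrast; it neither selects one contrast nor controls error across two.

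A second reply is that testing order and allocation of the error level usually sit in a statistical analysis plan, which is not shown here. That is fair for the detail. The primary time point, though, is part of the outcome definition, and this article fixes it as two. The article also describes itself, in section {31c}, as covering the whole trial.

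Two further inferences are tempting but unsupported.

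- *That the 6-month report is an undeclared interim look, at odds with* "Thus, no interim analyses are planned". That sentence rests on safety. Recruitment was scheduled to end in January 2024, so complete 6-month data would come after enrolment closed, and nothing lets them alter the trial.
- *That the 6-month paper will appear first, or that the favourable result could be reported alone.* The dissemination section lists the 6-month report first but sets no order of publication, and it commits to reporting mental health outcomes at both time points.

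**Conclusion.** The point holds in this form: the article fixes two primary time points against one 5% level and gives no rule joining them, so 5% is not guaranteed and the conclusion is undefined when the two results differ. The excess is conditional. It is about 7.8% to 9.1% if success at either time point counts and the test statistics correlate at 0.8 to 0.5, with 9.75% under independence. The either-one rule is a reading that the article leaves open, not one that it states; the correlation and the two-sided level are assumptions. The lack of a rule for discordant results depends on none of these assumptions.

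**What to change.** Before any outcome data are analysed, adopt one of the following:

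- name one primary time point for PHQ-9 change, test it at two-sided 5%, and test the other at 5% only if the first is significant; or
- name one joint or averaged contrast from the mixed model as the single primary comparison.

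State the rule in the abstract, in Outcomes {12} and in Statistical methods {20a}. In Sample size {14}, say which time point or contrast the 188 patients were powered for. Both articles should then identify their PHQ-9 result by its place in that rule.

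The investigators should choose the time point. They should note that the only attrition figure given is for 12 months and that the design is described as having one year of follow-up; if 6 months is chosen, the sample size assumptions need to be stated for it.

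The cost is a sentence in each of three places and one in the sample size section, with no additional patients or data. The downside of the ordered test is that the second time point is confirmatory only after a positive first test; a joint or averaged contrast gives up a separate confirmatory claim at each time point.
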